**Fig. 1 Fig1:**
[figure not shown]
Flowchart illustrating the participant pathway and corresponding data analysis. ITT, intent-to-treat; mITT, modified intent-to-treat

All data points and images are collected via an electronic data capture (EDC) system provided by REDCap Cloud (nPhase, Inc, version 1.7.3) using electronic case report forms (eCRFs) which contain constraints on data types and ranges, as well as alerts for inconsistent or missing data entry to ensure data validity, completeness, consistency, and uniformity. Additionally, further consistency checks are performed using data exports. All open queries are tracked and summaries are sent to the sites regularly. A regular remote monitoring scheme is employed for each participating site to verify data quality and identify potential issues regarding patient enrollment and data collection. While no on-site monitoring or source data verification is planned due to resource limitations, a Blinded Central Image Review (BCIR) will be used to assess selected outcome measures.

### Primary Outcome Measure

The primary outcome measure of CALCIO is a composite of wound healing and freedom from amputation at 12 months after the first IVL procedure. Wound healing is defined as the healing status of the dominant ischemic wound of the target limb as assessed by the investigators using the categories defined in Table 3.

**Table 3 Tab3:** Definitions of wound healing status

Wound healing	
Complete	Complete epithelialization of the wound persistent for at least 14 days
Partial	Decrease of wound size > 50% compared to baseline (in largest diameter)
Unchanged	Increase or decrease of wound size ≤ 50% compared to baseline (in largest diameter)
Worsening	Increase of wound size > 50% compared to baseline (in largest diameter)

Patients who presented no wound at baseline (Rutherford category 4) are followed for the development of de novo ischemic ulcers. If such an ulcer appears after treatment, the limb will be reported separately as “worsening.”

Freedom from amputation will be assessed by considering both minor (digital, metatarsal) and major (below or above the knee) amputations; however, amputations that had been planned before the first IVL treatment will be reported separately. For patients who receive an amputation, healing of the stump will be reported.

### Secondary Outcome Measures

#### Immediate Effectiveness

Immediate effectiveness, per treated segment, is defined as residual diameter stenosis ≤ 30% and will be assessed by BCIR using DSA images at the following time points: 1) after IVL and before any potential adjunctive intervention, “**technical success of IVL,**” and 2) by the end of the complete procedure after any potential, planned or unplanned, adjunctive intervention, “**overall procedural success.**”

#### Long-Term Effectiveness

To further assess the long-term effectiveness of IVL, **wound healing** and **freedom from amputation**, as defined above, will be reassessed at 24 months, and **amputation-free survival** will be reported from the time of the first IVL treatment, excluding patients with any amputation that had been planned beforehand.

Other secondary effectiveness outcome measures that will be assessed at 12 and 24 months include: i) changes of Rutherford category, limb perfusion, and WIfI score [16–18]; ii) **freedom from clinically driven target lesion revascularization (CD-TLR)**, defined as the absence of any endovascular re-intervention to the target segment (± 10 mm) or surgical bypass performed because of restenosis or occlusion and **CD-TLR-free survival**; and iii) patency of the target segments with a distinction between **primary patency** (absence of total occlusion without any re-intervention to the target segment); **assisted primary patency** (absence of total occlusion following re-intervention on the target segment due to restenosis); and **secondary patency** (absence of total occlusion following re-intervention on the target segment due to occlusion).

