## Statistical Analysis

CALCIO is a single-arm study that will use mainly descriptive statistics to report the outcome measures. The target of 400 participants was not determined through a formal sample size calculation but was assessed by the Steering Committee as a sufficiently large sample to provide meaningful information on the treatment’s effectiveness while remaining achievable within the planned enrollment period. All participants who were planned to receive IVL will be included in the intent-to-treat (ITT) population, regardless of whether they received the planned procedure. In contrast, the modified intent-to-treat (mITT) population will only include participants who received IVL treatment.

The results of the primary outcome measure will be presented using summary statistics and a 95% confidence interval (CI). For time-to-event outcome measures (amputation-free survival) and (CD-TLR-free survival), median time-to-event and 95% CI will be calculated using the Kaplan–Meier estimator, while the impact of different covariates will be assessed using a stratified log-rank test and an univariable Cox proportional hazard regression. Following that, covariates with *p* values < 0.1 and ≤ 20% missing data will be included in a multivariable Cox proportional hazards regression model, while variables with p values < 0.05 will be retained in the model after backward elimination or if they contribute to the predictability of the model. All variables that were not included in the model due to extensive missing data will be listed. All other statistical tests will be based on a significance level of 5%, and estimates will be presented using 95% bilateral CIs. No adjustment for multiple testing will be done. In the analyses of time-to-event outcomes, data will be censored at the last time the patients’ status was assessed.

In general, no imputation of missing data is planned for the analyses, and missing observations will be presented as a percentage of the total. However, for the primary outcome measure, depending on the number of deceased and lost-to-follow-up participants before 12 months, a sensitivity analysis may be performed.

Given the absence of planned confirmatory hypothesis testing, findings should be considered exploratory. The statistical analysis will be conducted using the latest available versions of R and RStudio.

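### Amputation-free survival drops every patient with a pre-planned amputation, so it describes a restricted subset of the treated cohort and omits that group's later deaths and unplanned amputations

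*Protocol article*

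**What the plan says.** The Protocol article, Long-Term Effectiveness, states that AFS "will be reported from the time of the first IVL treatment", "excluding patients with any amputation that had been planned beforehand". The same sentence says that wound healing and freedom from amputation, "as defined above, will be reassessed at 24 months". That points back to Primary Outcome Measure, where freedom from amputation is assessed by "considering both minor (digital, metatarsal) and major (below or above the knee) amputations", with the proviso that "amputations that had been planned before the first IVL treatment will be reported separately".

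Statistical Analysis defines two populations. ITT is everyone planned for IVL, and "the modified intent-to-treat (mITT) population will only include participants who received IVL treatment". Neither definition mentions planned amputation, and no separate set is named for AFS. Table 1 does not list a planned amputation as an exclusion criterion, so these patients can be enrolled, treated and followed.

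**The concern.** There is a sound reason to treat planned amputations specially: an amputation decided before IVL is not a failure of IVL. Setting aside that one procedure is enough to achieve this. The AFS rule goes further and removes the patient, together with everything that happens to that patient afterwards.

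Three things are at stake.

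- **Population.** The study is presented as evidence on real-world CLTI practice. Its outcome combining limb loss and death would cover only part of the treated cohort.
- **Events.** Later deaths and unplanned amputations in the excluded patients cannot enter the Kaplan-Meier estimate or the Cox models for AFS.
- **Comparability.** AFS and freedom from amputation at 12 and 24 months may rest on different denominators, yet readers will set them side by side.

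Deaths deserve particular attention. The Safety section limits its outcome to events within 30 days, which leaves AFS as the main named outcome that would carry later mortality.

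**Working it through.** **Stated figures.** The article gives no expected AFS, event count or power figure, and "The target of 400 participants was not determined through a formal sample size calculation". There is nothing to reproduce. The definitions are compared first; the numbers after that are illustrative.

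**Definitions side by side**

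| | Freedom from amputation (12 and 24 months) | AFS |
|---|---|---|
| Planned amputation | That amputation is reported separately | The patient is excluded |
| Amputation level that triggers the rule | Not restricted; minor and major both count | Any |
| Part of ITT or mITT definition | No | No |

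I read AFS in its usual sense, with death or amputation as the event. Digital amputations count, so a single planned toe amputation is enough for exclusion. The censoring rule ("data will be censored at the last time the patients’ status was assessed") does not help, because an excluded patient contributes no follow-up to censor.

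**Illustration 1: hazard ratio.** Let f be the share of patients with a planned amputation, S the AFS in the rest, and HR the hazard ratio for death or a non-planned amputation in the excluded group. Then

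AFS(all) = (1 − f) × S + f × S^HR, and overstatement = S − AFS(all).

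All inputs are assumptions: S = 0.85 at 12 months; with constant hazards, S = 0.85² = 0.7225 at 24 months; f = 0.10 to 0.30; HR = 1.5 to 3.

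- 12 months, f = 0.10, HR = 1.5: 0.90 × 0.85 + 0.10 × 0.7837 = 0.843. Overstatement 0.7 points.
- 12 months, f = 0.30, HR = 3: 0.70 × 0.85 + 0.30 × 0.6141 = 0.779. Overstatement 7.1 points.
- 24 months, f = 0.10, HR = 1.5: 0.90 × 0.7225 + 0.10 × 0.6141 = 0.712. Overstatement 1.1 points.
- 24 months, f = 0.30, HR = 3: 0.70 × 0.7225 + 0.30 × 0.3771 = 0.619. Overstatement 10.4 points.

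**Illustration 2: relative risk.** With event risk p in the rest and relative risk RR in the excluded group, the overstatement is f × p × (RR − 1). These inputs are also assumed.

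- f = 0.05, p = 0.20, RR = 1.5: 0.05 × 0.20 × 0.5 = 0.5 points.
- f = 0.05, p = 0.30, RR = 2: 0.05 × 0.30 × 1 = 1.5 points.
- f = 0.30, p = 0.30, RR = 2: 0.30 × 0.30 × 1 = 9.0 points.

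For comparison, the simple binomial 95% half-width, 1.96 × √(p(1 − p)/n) with n = 400 × (1 − f), runs from 4.0 points (n = 380, p = 0.20) to 5.4 points (n = 280, p = 0.30). A small excluded share gives a bias well inside sampling error. A large share at clearly higher risk gives one outside it.

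**Equal risk.** With RR = 1 there is no bias, but events are still lost. At f = 0.20 and p = 0.30, 400 × 0.20 × 0.30 = 24 of 400 × 0.30 = 120 events leave the Cox models.

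**The case against.** The exclusion is prespecified, openly stated and has a rationale. AFS is a secondary outcome in a single-arm, mainly descriptive study that calls its findings exploratory, so no hypothesis test is affected. This stands, and it limits the stakes to interpretation and comparability.

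A reader might infer more than the document supports in five ways.

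- **A flat contradiction with the primary outcome.** Reporting planned amputations separately suggests that only the event is set aside. The article does not say whether the patient stays in the denominator as event-free or is shown as a separate group. The AFS exclusion is explicit; the mismatch with freedom from amputation is likely but not settled.
- **Upward bias as a fact.** The article states neither how many patients have a planned amputation nor that they are at higher risk. Higher risk is a reasonable clinical inference, but the direction of the bias depends on it.
- **Events lost from the whole study.** They are lost from AFS. Later unplanned amputations may still appear under freedom from amputation. CD-TLR-free survival carries no such exclusion, although the article does not say whether death counts there. Deaths before 12 months may also enter a sensitivity analysis of the primary outcome.
- **Labelling an amputation as planned after the fact.** The baseline list under Data Collection and Quality Control does not mention planned amputation, but that list is a condensed account of the case report form. Both rules tie the label to planning before the first IVL. Nothing indicates retrospective labelling.
- **Comparison with the 98% in the Discussion.** That figure is freedom from major amputation, reported beside 89% overall survival. It is not an AFS figure and is no benchmark here.

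**Conclusion.** The point holds as a matter of definition. AFS is restricted at patient level by a rule outside the ITT and mITT definitions, and the excluded patients' later deaths and unplanned amputations cannot enter it. The restricted population and the lost events follow from the text alone. The difference in denominators is probable.

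The direction and size of any bias rest wholly on assumptions. Under the first set, AFS is overstated by about 0.7-7 points at 12 months and 1-10 points at 24 months. Under the second, with a 5-30% share excluded, event risk of 0.20-0.30 and relative risk of 1.5-2, it is overstated by 0.5-9 points. If the excluded patients have the same risk, there is no bias, only lost events and precision. The change should be made, with moderate confidence, because setting aside only the planned procedure serves the same aim and keeps the cohort whole.

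**What to change.** Analyse AFS in all treated (mITT) patients from the first IVL. Do not count the specific amputation planned before that procedure as an event; count death and any other amputation. State the same event-level rule for freedom from amputation at 12 and 24 months, so that the outcomes share a denominator. Present AFS under the article's exclusion as a sensitivity analysis, with the number of patients excluded.

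The cost is analysis-plan wording and a site query confirming which procedure was planned before the first IVL. Follow-up is expected to run to July 2028, so there is time. The downside for the sponsor is that AFS may look somewhat less favourable.

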#### Safety

Safety of IVL will be assessed by monitoring the incidence and severity of major adverse events (AEs) within 30 days after the procedure. These include, but are not limited to, procedural complications at the target and access sites (flow-limiting dissection, emboli, occlusion, infection, hematoma, false aneurysm, and perforation); deterioration of renal function; allergic reaction; sepsis; acute onset of limb ischemia; stroke and myocardial infarction. Severity will be graded according to the CIRSE classification system [19]. The total number of AEs and the percentage of patients with at least one AE will be summarized for AEs of i) any grade, ii) grade 3–4, and iii) grade 5. A further distinction will be made based on the likelihood of a causal relationship between the AE and the IVL procedure, as assessed by the PIs.

#### Patient-Reported Health-Related Quality of Life

Patient-reported HRQoL will be evaluated using the EuroQol questionnaire EQ-5D-5L. This questionnaire includes 5 dimensions (mobility, self-care, usual activities, pain or discomfort, and anxiety or depression), each having 5 response levels (no problems, slight problems, moderate problems, severe problems, unable to/extreme problems) as well as a vertical visual analog scale (EQ VAS) from 1 to 100 for the patients to rate their general health. The number and percentages of responses per dimension will be analyzed and reported together with the mean, standard deviation, median, maximum, and minimum values of the EQ VAS.

#### Change in Vascular Calcification

The visualization and quantification of potential changes in local vascular calcification immediately following IVL will be investigated as an exploratory outcome. For this purpose, non-contrast images of the target segments taken from unsubtracted mask of DSA images pre- and post-IVL will be collected and analyzed by BCIR.

## Statistical Analysis

CALCIO is a single-arm study that will use mainly descriptive statistics to report the outcome measures. The target of 400 participants was not determined through a formal sample size calculation but was assessed by the Steering Committee as a sufficiently large sample to provide meaningful information on the treatment’s effectiveness while remaining achievable within the planned enrollment period. All participants who were planned to receive IVL will be included in the intent-to-treat (ITT) population, regardless of whether they received the planned procedure. In contrast, the modified intent-to-treat (mITT) population will only include participants who received IVL treatment.

The results of the primary outcome measure will be presented using summary statistics and a 95% confidence interval (CI). For time-to-event outcome measures (amputation-free survival) and (CD-TLR-free survival), median time-to-event and 95% CI will be calculated using the Kaplan–Meier estimator, while the impact of different covariates will be assessed using a stratified log-rank test and an univariable Cox proportional hazard regression. Following that, covariates with *p* values < 0.1 and ≤ 20% missing data will be included in a multivariable Cox proportional hazards regression model, while variables with p values < 0.05 will be retained in the model after backward elimination or if they contribute to the predictability of the model. All variables that were not included in the model due to extensive missing data will be listed. All other statistical tests will be based on a significance level of 5%, and estimates will be presented using 95% bilateral CIs. No adjustment for multiple testing will be done. In the analyses of time-to-event outcomes, data will be censored at the last time the patients’ status was assessed.

In general, no imputation of missing data is planned for the analyses, and missing observations will be presented as a percentage of the total. However, for the primary outcome measure, depending on the number of deceased and lost-to-follow-up participants before 12 months, a sensitivity analysis may be performed.

Given the absence of planned confirmatory hypothesis testing, findings should be considered exploratory. The statistical analysis will be conducted using the latest available versions of R and RStudio.

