**Methods:**

CALCIO is a worldwide, multicenter, prospective cohort study designed to follow for 2 years 400 participants treated with the Shockwave Medical IVL System. Eligible patients, adults (≥ 18 years) with CLTI (Rutherford category ≥ 4) and calcified femoro-popliteal and/or crural lesions visible on fluoroscopy, are recruited upon providing informed consent. The primary outcome measure is a composite of wound healing and freedom from amputation at 12 months. Secondary outcome measures include technical success, amputation-free survival, changes in Rutherford category, limb perfusion and wound, ischemia, and foot infection (WIfI) score, patency, need for revascularization, safety, and patient-reported health-related quality of life (HRQoL). Results will be reported using mainly descriptive statistics. Patient enrollment opened in July 2024 and is planned to continue until July 2026, with the follow-up period expected to end in July 2028.

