## Data Collection and Quality Control

Baseline data, obtained within 6 weeks before the first planned IVL treatment, include demographics (age and sex) and relevant medical history (smoking habit, diabetes, hypertension, hyperlipidemia, symptomatic ischemic heart disease, ongoing anti-platelet/anti-coagulation treatment). Data specific to the target limb, including the presence and extent of ischemic ulcers and foot infection, measurement of limb perfusion (ankle–brachial index, ankle systolic pressure, toe pressure, or transcutaneous oximetry), and history of prior surgical or endovascular treatments for PAD, as well as data specific to the target segments, such as location, degree of stenosis, and length of occlusion (if relevant), are also captured. Upon completion of the first IVL treatment, procedural details, including information on any potential adjunctive intervention, are collected for each target segment together with digital subtraction angiography (DSA) images and non-contrast images taken from the unsubtracted mask of DSA images. In case patients do not receive IVL as planned, reasons for not proceeding with the planned treatment are recorded, and data collection is suspended (Fig. 1). For all treated patients, follow-up data are collected at 6, 12, and 24 months. Safety data are collected from the first IVL procedure throughout the study, and HRQoL is planned to be captured at each visit.

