## Discussion

IVL is a relatively recent technology with an expanding evidence base in claudicant patients demonstrating a favorable safety profile and significant luminal gain in calcified lesions; however, evidence in patients with CLTI remains limited. A recent single-center retrospective study on CLTI patients receiving IVL plus drug-coated balloon reported promising 12-month outcomes, with 92% freedom from CD-TLR, 98% freedom from major amputation, and 89% overall survival [20].

Despite the consensus that vascular calcification hinders clinical outcomes of endovascular interventions, European and American guidelines on the management of PAD offer limited, non-specific direction on revascularization strategies for severely calcified lesions and do not consistently address IVL or other plaque-modifying techniques [1, 2]. Reimbursement for IVL remains variable across healthcare systems, which likely constrains routine adoption.

In the UK, however, the National Institute for Health and Care Excellence (NICE) released its guidance on IVL for calcified arteries in PAD in 2024 (www.nice.org.uk/guidance/ipg780). Acknowledging “an unmet need for a safe and effective endovascular option for treating heavily calcified arterial lesions when surgery is unsuitable,” the NICE recommendations state that IVL can be used with special arrangements for clinical governance, consent, and audit or research. The existence of such guidelines is directly reflected in clinical practice, as a larger number of patients have access to the procedure in the UK compared to other countries. However, while the NICE guidance is based on the conclusion that IVL is safe and associated with a reduced need for stenting, it also highlights a lack of evidence regarding long-term patient outcomes. NICE specifically encourages further research to include details on patient selection (including lesion location and stenosis severity), adjunctive interventions, the need for repeat revascularization, patient-reported quality of life, amputation, and mortality.

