Designed to specifically address these evidence gaps, CALCIO intends to complement the existing literature by collecting prospective data on the use of IVL in real-world CLTI practice. The findings are expected to contribute to future discussions on the role of IVL in clinical guidelines and inform reimbursement considerations for its use in CLTI patients. The study was received very positively by the community, with over 50 sites expressing interest in participating.

Patient enrollment for CALCIO opened in July 2024 and is planned to continue until July 2026. The follow-up period is expected to end in July 2028. At the time of manuscript submission, 38 sites from 8 countries, including 14 in the UK, were participating in the study and 357 patients had been enrolled, including 182 in the UK.

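### The two time-to-event outcomes are to be summarised by a Kaplan–Meier median that 24 months of follow-up will very probably not reach for CD-TLR-free survival, and may not reach for amputation-free survival

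*Protocol article*

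**What the plan says.** In the Statistical Analysis section of the protocol article, the summary named for both time-to-event outcomes is the median: "median time-to-event and 95% CI will be calculated", by the Kaplan–Meier method. Covariate effects are then examined by log-rank tests and Cox regression. No Kaplan–Meier probability at a fixed time is named, and nothing is said about an unreached median.

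The horizon is fixed elsewhere. The abstract describes a study "designed to follow for 2 years 400 participants". Under Data Collection and Quality Control, "follow-up data are collected at 6, 12, and 24 months". In the Discussion, "The follow-up period is expected to end in July 2028", two years after the planned close of enrollment in July 2026. Under Statistical Analysis, "data will be censored at the last time" at which status was assessed. There is therefore essentially no information beyond 24 months.

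Table 2 lists both composites only as time-to-event measures. The Long-Term Effectiveness section, however, places CD-TLR-free survival among the measures to be assessed at 12 and 24 months. It gives amputation-free survival no fixed time point and excludes patients whose amputation was planned before treatment.

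The article's only event rates for patients with CLTI treated by IVL are 12-month background figures in the Discussion: "92% freedom from CD-TLR, 98% freedom from major amputation, and 89% overall survival". Their source is described as "A recent single-center retrospective study on CLTI patients receiving IVL plus drug-coated balloon".

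**The concern.** A Kaplan–Meier median can be read off only if the curve falls to 50% within follow-up. When fewer than half of patients have the event in two years, the estimate is reported as not reached, without an upper limit and often without a lower one. That is a valid result, but it says little. It cannot be set beside the 12-month proportions that the article cites, and it does not tell a guideline or reimbursement body what share of patients remain event-free.

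An article may leave much detail to an unseen analysis plan. Here it chooses a specific estimate, and that choice fits the study's horizon badly. It also does not carry through the 12- and 24-month assessment that the Long-Term Effectiveness section promises for CD-TLR-free survival.

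**Working it through.** The article contains no event-rate or sample-size calculation, so there is no figure of its own to reproduce. The check asks where the curves would stand at 24 months under the rates it quotes.

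**Inputs.** From the Discussion, at 12 months: freedom from CD-TLR 0.92, freedom from major amputation 0.98, overall survival 0.89. From the abstract: 400 participants, 2 years each. Assumed: constant hazard, so S(24) = S(12)² and median = 12 × ln(0.5) / ln(S(12)) months.

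**Threshold.** A median by 24 months needs S(12)² ≤ 0.5, that is S(12) ≤ √0.5 = 0.707.

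**Combining the components.** Independence gives the product a × b. Whatever the dependence, the 12-month composite lies between a + b − 1 and the smaller of the two.

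| Outcome | Combination | S(12) | S(24) | Implied median (months) |
|---|---|---|---|---|
| CD-TLR-free survival | 0.92 × 0.89 | 0.819 | 0.670 | 41.6 |
| | lower bound, 0.92 + 0.89 − 1 | 0.810 | 0.656 | 39.5 |
| | upper bound | 0.890 | 0.792 | 71.4 |
| AFS, major amputation only | 0.98 × 0.89 | 0.872 | 0.761 | 60.8 |
| | lower bound, 0.98 + 0.89 − 1 | 0.870 | 0.757 | 59.7 |
| | upper bound | 0.890 | 0.792 | 71.4 |

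If deaths are not counted as events in CD-TLR-free survival, S(24) = 0.92² = 0.846 and the median is about 100 months. The conclusion for that outcome does not depend on the reading.

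**Sampling variation.** Kaplan–Meier curves were simulated with n = 400, censoring at 24 months and assumed dropout of 0, 10 or 20% per year, 2,000 runs per setting. At S(12) = 0.872, 0.819 and 0.81, neither the median nor its lower 95% limit was reached in any run.

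**What would overturn this.** Under independence:
- A higher hazard throughout: ln(0.5) / ln(S(24)) gives 1.7 times the quoted level for CD-TLR-free survival and 2.5 times for AFS.
- A higher hazard in year 2 only: ln(0.5 / S(12)) / ln(S(12)) gives about 2.5 times and 4.1 times the year-1 hazard.

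**Minor amputations.** The Primary Outcome Measure section counts minor and major amputations; the quoted 98% covers major only. No minor-amputation rate is given, so a range is shown, with S(12) = 0.872 × (1 − m):

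| Assumed 12-month risk m | 0% | 5% | 10% | 15% | 20% | 25% |
|---|---|---|---|---|---|---|
| AFS at 24 months | 0.76 | 0.69 | 0.62 | 0.55 | 0.49 | 0.43 |
| Median (months) | 61 | 44 | 34 | 28 | 23 | 20 |

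The break-even is 1 − 0.707 / 0.872 = 0.189, about 19% in year 1, assuming minor amputation is independent of the other events. If no patient had more than one of the three events, it would be lower: 0.870 − 0.707 = 0.163, about 16%.

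**The alternative estimate.** With n = 400, no dropout and SE = √(S(1 − S) / 400), the 24-month probabilities would be about 0.67 (95% CI 0.62 to 0.72) for CD-TLR-free survival and 0.76 (0.72 to 0.80) for AFS with major amputation only.

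**The case against.** The strongest reply is that little is lost. The Kaplan–Meier curve itself contains the 12- and 24-month probabilities. The log-rank and Cox analyses do not need a median. Freedom from amputation and CD-TLR are planned at 12 and 24 months, and naming a median does not forbid other estimates. All of this stands, and it limits the severity. A reader might infer that two long-term outcomes are left without any usable figure; the documents do not support that.

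The quoted rates are also background, not planning assumptions. They come from one center and one treatment combination, whereas this study sets no treatment restrictions and expects about 40 sites. That stands as a caveat. The margin for CD-TLR-free survival is nevertheless wide, since the hazard would have to be about 1.7 times the quoted level throughout.

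For amputation-free survival the objection is stronger. A reader might infer from the 61-month figure that this median is equally out of reach. That figure belongs to a narrower endpoint, major amputation or death. With minor amputations counted, and a rate that the article does not give, the median could fall inside 24 months. Excluding patients with pre-planned amputations lowers the risk by an unknown amount.

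A reader might also infer that a median reached late would rest on a thin, heavily censored tail. The design does not support this. Every participant is planned for a full 24 months, so staggered entry shortens nobody's planned follow-up. If the curve neared 50% just before the last visit, about 200 of 400 would still be at risk without dropout, or about 400 × 0.5 × 0.9² = 162 with an assumed 10% annual dropout.

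**Conclusion.** The concern holds in limited form. For CD-TLR-free survival the named summary will very probably not be reached: about 67% would be event-free at 24 months, 66% to 79% under any dependence between CD-TLR and death. This rests on one study's 12-month rates and a constant hazard. For amputation-free survival the same follows if only major amputations are counted (about 76% at 24 months). As the study defines amputation, the answer turns on an unstated minor-amputation rate, with a break-even near 19% in year 1 under independence.

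Nothing is biased, the primary outcome is untouched, and other planned analyses still inform on both outcomes. The outcomes are secondary, and the article itself treats its findings as exploratory. Severity is minor. It is still worth correcting, because the better estimate costs nothing and the Statistical Analysis section does not match the Long-Term Effectiveness section for CD-TLR-free survival.

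**What to change.** In the Statistical Analysis section, or the analysis plan if it repeats that wording, name the Kaplan–Meier event-free probabilities at 12 and 24 months, with 95% CI and numbers at risk, as the main summary for both outcomes. Report the median only if it is reached. Align Table 2 and the Long-Term Effectiveness section so that both composites carry the same time points.

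The cost is one sentence and a table entry. No visits, data items or participants are added. Follow-up is expected to run to July 2028, so the change can be recorded well before the final analysis.
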